### Experimental intervention

2.5

The experimental intervention consists of (partial) CN or any ablative local therapy between 6 mo and 1.5 yr after the start of systemic treatment. All types of ablative local therapies are allowed as a substitute for CN, including magnetic resonance imaging–guided stereotactic radiation. The patients’ physician chooses the treatment plan and the modality used for tumour ablation. Randomisation occurs after at least 6 mo of ICI combination therapy, as stated in Figure 2. Patients who discontinue their first-line treatment due to progression at metastatic sites in the timeframe between randomisation and local therapy are disqualified for local treatment but continued in the TwiCs study in order to be part of the intention-to-treat (ITT) analysis. The same applies for patients who are randomised to the experimental arm but who refuse local treatment. All these patients will be treated according to the SOC. Patients in the experimental arm will be asked for additional sampling of blood after the local intervention.

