### Primary and secondary endpoints

2.2

The primary clinical endpoint is OS, defined as the time from randomisation to death of any cause. The main secondary endpoint is the objective response rate in the primary tumour before local therapy, assessed by a computed tomography scan. Other secondary endpoints are long-term follow-up of quality of life (QoL) using the Dutch validated European Organisation for Research and Treatment of Cancer (EORTC) Quality of Life Questionnaire (QLQ-C30) [27] and Clavien-Dindo classification of surgical morbidity [28]. Both follow-up of QoL and surgical morbidity are part of the standard PRO-RCC data collection schedule.

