### Eligibility criteria

2.4

At enrolment in the PRO-RCC cohort, patients are asked to provide informed consent for prospective collection of clinical, survival, and QoL data. In addition, on entry in the cohort, we ask patients to consent for possible future randomisation in TwiCs studies (staged informed consent procedure) [29]. Herein, patients are informed that, when a TwiCs study to investigate the efficacy of a new experimental intervention is initiated, they will be offered that experimental intervention if they are selected randomly for the experimental intervention group. They are also advised that they will not be informed about the TwiCs study when selected randomly for the control group but that their data will be used as in the trial context. Patients within the PRO-RCC cohort who meet the PrimerX inclusion criteria, as mentioned in Table 1, form a subcohort of eligible patients. Within this subcohort, patients without progression at metastatic sites, with the primary tumour in site (irrespectively of the size of the tumour), following at least 6 mo of any of the standard first-line ICI combination therapies, are allocated randomly to either the experimental arm or the control arm in a 1:1 ratio, until the calculated sample size is reached or early stopping rules are met. Patients who have progression in the primary tumour only are also eligible for trial participation. Since patients are randomised at different time points, between 6 and 18 mo after the start of systemic treatment, the timing of randomisation is added as a variable when conducting the analysis.

**Table 1 t0005:** Inclusion criteria

Male or female patients age ≥18 yr
Signed and written informed consent obtained; note: written and signed informed consent will be obtained before any study procedures, including study‐specific-screening procedures
Informed consent obtained for being offered future experimental interventions within the PRO-RCC project
Histologically confirmed diagnosis of metastatic clear cell, papillary, or chromophobe renal cell carcinoma of intermediate to poor risk, including sarcomatoid features
World Health Organization performance status of 0–1
Surgical candidates based on surgeon and anaesthetist assessment
Treatment with an IO combination (IO + IO or IO + TKI) as standard of care for metastatic RCC for at least 6 mo
Absence of progression at metastatic sites at the time of identification (6 mo after the start of systemic first-line treatment)

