### Sample size calculation and Bayesian adaptive design

2.7

Estimation of the median OS of the selected subcohort for PrimerX is not trivial. Based on the CARMENA trial, synchronous mRCC patients treated with sunitinib without CN have median OS of 18.4 mo. All CARMENA patients were treated with VEGFR TKIs only, as ICI combination therapy was not available at the time. In these patients, a reduction in the hazard of death of 20–40% (if they would have been treated with ICI combination therapy, based on the CheckMate-214 study) would have resulted in median OS of 24–28 mo. This is in line with the post hoc OS analysis of mRCC patients with the primary tumour in place in the CM-214 study [30]. This demonstrated median OS of 26.1 mo (95% confidence interval [CI] 14–35 mo) for the ipilimumab + nivolumab arm versus 14.3 mo (95% CI 9.7–23 mo) for the sunitinib arm.

We therefore assume that the median OS for IMDC intermediate/poor-risk synchronous mRCC patients may be up to 28 mo. As in the PrimerX study patients with early systemic disease progression (within 6 mo) are excluded from participation, we estimate that the remaining patients have median OS of 36 mo, when treated with the SOC. The median OS of 36 mo comes down to an event rate per week (lambda) of 1 – (0.5^[1/156 wk]) = 0.0044. We believe that a meaningful deferred local therapy should reduce the hazard of death by at least 25% compared with the SOC (hazard ratio [HR] of 0.75), that is, a 12-mo survival benefit. This would balance the additional treatment burden of local therapy and would result in a median excess in OS of 48 mo in the experimental arm. Furthermore, we estimate that one out of six patients (15%) who are randomised to the experimental arm will refuse any form of local therapy and will therefore be treated by the SOC instead. This noncompliance reduces the measured benefit in an ITT analysis. In addition, a number of patients in the control arm will undergo CN. This also reduces the measured benefit. Based on our 2018–2020 IKNL dataset, we estimate that such “control dilution” will occur in approximately 7% of the cases, as over this period 60 out of 754 synchronous mRCC patients underwent deferred CN. Both noncompliance and control dilution reduce the anticipated HR from 0.75 to 0.7975. After correcting for control dilution, the lambda of the control arm drops from 0.0044 to 0.0043.

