In the Bayesian model, we used weakly informative conjugate gamma priors for the control hazard rate and weakly informative conjugate normal priors for the log-HR. Parameters for the prior distribution of the hazard rate were chosen such that these mirror the hazard rate of the control arm. The prior distribution for the log-HR had a mean of 0 and standard deviation of 5, which is considered to be a weak prior. All scheduled interim analyses estimate the Bayesian posterior probability of an HR of <0.9, and the corresponding stopping boundaries are listed in Table 2. For example, after 350 patients have been randomised, the trial will stop for futility if the posterior probability for HR <0.9 drops below 0.06. With these settings, 10 000 trial simulations were performed in FACTS (5000 for the scenario under the null hypothesis with HR = 1 and 5000 under the alternative scenario with HR = 0.7975). The results of these simulations revealed that the Bayesian empirical type I error rate of the trial was 5.6% and that the empirical power was 76%, to detect a Bayesian posterior probability of ≥75% for an HR of <0.9, during the final analysis under the alternative hypothesis. Importantly, the final one-sided frequentist log-rank test had a power of 79.8% under the alternative hypothesis that the HR is <1 (as opposed to <0.9 in the Bayesian interims) and a frequentist type I error rate of 4.9%. The average sample size was 548.6 in case of an HR of 1 and 596.8 in case of an HR of 0.7975. Notably, a standard two-arm trial without interim analyses would require 700 patients in total.

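### The power simulation makes no stated allowance for the permitted delay of up to 12 months between randomisation and local therapy

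*Protocol article*

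**What the plan says.** Section 2.2 makes the primary endpoint "OS, defined as the time from randomisation to death of any cause". Section 2.5 sets the earliest allocation: "Randomisation occurs after at least 6 mo of ICI combination therapy". It then defines the treatment window from a different origin: "The experimental intervention consists of (partial) CN or any ablative local therapy between 6 mo and 1.5 yr after the start of systemic treatment". Section 2.4 confirms that allocation times vary: "Since patients are randomised at different time points, between 6 and 18 mo after the start of systemic treatment".

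The protocol knows that there is a gap. Section 2.5 says that patients who stop first-line treatment "due to progression at metastatic sites in the timeframe between randomisation and local therapy are disqualified for local treatment", and it keeps them in the intention-to-treat analysis.

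Section 2.7 starts from the view that a worthwhile local therapy "should reduce the hazard of death by at least 25% compared with the SOC (hazard ratio [HR] of 0.75"). It moves this to 0.7975 for two reasons only: 15% refusal in the experimental arm and 7% nephrectomy in the control arm. The alternative is simulated as a single HR of 0.7975 with a control hazard of 0.0043 per week. The reported result is that "the final one-sided frequentist log-rank test had a power of 79.8% under the alternative hypothesis".

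**The concern.** Between randomisation and local therapy, the experimental arm receives the same care as the control arm. Unless the offer alone changes survival, the HR in that interval is 1. Deaths in the interval carry no treatment contrast, yet they count in the final log-rank test and in every Bayesian interim.

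The interims are the more exposed part. They are triggered by the number randomised, so each one includes recently allocated patients who may still be waiting.

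Some gap is built into the design, because counselling and the second consent follow allocation (section 2.4). The safeguards would not detect its effect: interim checks 1 and 2 look at noncompliance and control dilution, and the 1000-patient contingency rests on the same two quantities. The timing variable in section 2.4 describes when randomisation happens, not how long treatment takes to follow. At stake is a trial that stops for futility, or ends negative, more often than stated although the therapy works as assumed.

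**Working it through.** **Inputs from the protocol.** HR 0.7975; control hazard 0.0043/week; 1:1 allocation, maximum 700; interims at 250, 350, 450, 550 and 650 with the Table 2 limits on P(HR < 0.9); normal prior on log HR with mean 0 and SD 5; final one-sided 5% log-rank test after 5 years' follow-up.

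**Assumptions.** Accrual rate (not given; varied); delay distribution (not given; varied); effect starts on the day of local therapy; no other dropout; no excess perioperative mortality; normal approximation to the posterior; a futility stop counts as failure.

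**1. Is there room for delay in 0.7975?** Mixing hazards with 15% refusal and 7% control nephrectomy:
- experimental arm: 0.85 × 0.75 + 0.15 = 0.7875
- control arm: 0.93 + 0.07 × 0.75 = 0.9825
- ratio: 0.7875 / 0.9825 = 0.80

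For the contingency scenario (25% and 15%): (0.75 × 0.75 + 0.25) / (0.85 + 0.15 × 0.75) = 0.8125 / 0.9625 = 0.844, against 0.84 in section 2.7. The two named corrections account for the whole shift, with nothing left for delay.

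**2. Fixed-design check.** Events needed = 4(z₀.₉₅ + z_power)² / (ln HR)². For 79.8% power: 4 × (1.645 + 0.834)² / (0.2263)² ≈ 481. With 700 patients, 2 years' accrual and 5 further years, about 487 events are expected and power is 80.3%. This agrees with a constant HR and a maximum of 700.

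**3. Reproducing the adaptive design.** Constant HR from randomisation, 100 patients/year, 10,000 simulated trials per scenario:

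| | Published | Reproduced |
|---|---|---|
| Power, final log-rank | 79.8% | 79.4% |
| Type I error | 4.9% | 4.8% |
| Average N, HR 1 | 548.6 | 542 |
| Average N, HR 0.7975 | 596.8 | 592 |

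Power is 81.8% at 75/year and 77.9% at 120/year. The average sample sizes fit slightly better at 120/year (547 and 595), and power fits better at 100/year.

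**4. Adding the delay.** With delay D, control hazard λ and a unit exponential draw E, a patient in the experimental arm dies at E/λ if that is no later than D, and otherwise at D + (E − λD)/(λ × 0.7975). Where two figures are shown, they come from separate runs at 100/year.

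| Delay, randomisation to local therapy | Power at 100/yr | Loss from 79.4% (points) |
|---|---|---|
| none | 79.4% | – |
| 4 weeks | 77.7% | about 2 |
| 8 weeks | 75.4–76.3% | 3–4 |
| 3 months for all | 72.0–72.6% | about 7 |
| uniform over 0–6 months | 73.4% | 6 |
| randomised evenly over 6–18 months, treated evenly over the remaining window (mean 3 months) | about 73–74% | 6–7 |
| uniform over 0–12 months | 66.4–67.5% | 12–13 |
| 12 months for all | 53.1% | 26 |

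The losses depend only modestly on accrual. For 8 weeks they are 81.8 − 78.4 = 3.4 points at 75/year and 77.9 − 73.5 = 4.4 at 120/year. For delays uniform over 0–12 months they are 81.8 − 70.9 = 10.9 and 77.9 − 64.3 = 13.6. At 100/year, average N under the alternative rises from 592 to about 604 with a 3-month delay.

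**The case against.** Section 2.8 describes the intention-to-treat result as the average causal effect of treatment that is offered. On that view 0.7975 could be an average HR from randomisation, with waiting time included. The reproduction shows how the design was probably simulated, not what 0.7975 was meant to represent. This stands as a possibility, and the fix leaves room for it. But section 2.7 names only two corrections, and step 1 shows that they use up the whole shift from 0.75.

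The reproduction is also not proof that no lag was simulated. With 75 patients/year, a 4-week lag gives 79.8% as well, although average N under HR 1 is then 534, further from 548.6. Figure 2, to which section 2.5 refers for timing, is not shown, and the full protocol may hold the accrual rate and other simulation settings.

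The flexible timing is deliberate. The Discussion says that the trial is not suited to finding the best time point and that complexity harms accrual in surgical trials. Surgical candidacy is judged at inclusion, which makes long routine waits less likely. Both points stand, but neither puts a delay into the power figure.

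A reader might infer that the 79.8% is simply not delivered, or that true power lies between the low 50s and the high 60s. The documents do not support either. A 12-month gap needs randomisation at 6 months and treatment at 18. A uniform 0–12 month delay would need everyone randomised at 6 months, whereas section 2.4 spreads randomisation over 6 to 18 months. With a 4-week delay the loss is only about 2 points.

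**Conclusion.** The protocol permits a gap of up to 12 months between the start of the survival clock and local therapy, and the described power inputs make no allowance for it. If local therapy has no effect before it is given and 0.7975 applies afterwards, any delay lowers power. The loss is about 2 points at 4 weeks, 3 to 4 at 8 weeks and 6 to 7 at a mean of 3 months; 12 to 13 points is near the worst case. The direction is certain under those conditions. The size rests on an assumed delay and an assumed accrual of about 100 per year, and the losses are steadier than the absolute power values. Patients who lose local therapy through progression in the gap are not modelled and would lower power further.

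The validity of the trial is not in question. If the true HR is 1 throughout, delay changes nothing, so the type I error and the intention-to-treat log-rank test are unaffected. What needs correcting is the stated operating characteristics.

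**What to change.** In section 2.7:
- State the expected distribution of time from randomisation to local therapy.
- Rerun the FACTS simulations with HR 1 up to that delay and the assumed HR afterwards, or justify 0.7975 as the average HR from randomisation.
- Replace the 79.8% log-rank power, the 76% Bayesian power and the average sample sizes with the results.

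In section 2.7 and Table 2, add observed time from randomisation to local therapy to interim checks 1 and 2, beside noncompliance and control dilution.

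The sponsor should also reconcile the treatment window in section 2.5 with what the simulation assumes. No rule on the timing of treatment is proposed here.

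The cost is one rerun of existing simulations, one more item to report at the early checks, and probably a less favourable stated power. Restoring 80% would need more events, and whether to seek them is the sponsor's decision once the figures are known.

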**Fig. 2 f0010:**
[figure not shown]
Overview of PrimerX TwiCs experimental arm including randomisation, follow-up, and procedure in case of progression. CN = cytoreductive nephrectomy; ICI = immune checkpoint inhibitor; TwiCs = Trial within Cohorts.

### SOC treatment

2.6

Patients randomised to the control arm will receive first-line ICI combination therapy according to current guidelines, which do not routinely recommend CN in this setting [20]. Patients with controlled systemic disease but progression of the primary tumour can be offered deferred CN at the discretion of the treating physician. Likewise, patients with a complete response at metastatic sites who can be rendered disease free by deferred CN are not excluded from an intervention if the treating physician considers nephrectomy in the patient’s best interest. These patients remain in the TwiCs study for the ITT analysis.

### Sample size calculation and Bayesian adaptive design

2.7

Estimation of the median OS of the selected subcohort for PrimerX is not trivial. Based on the CARMENA trial, synchronous mRCC patients treated with sunitinib without CN have median OS of 18.4 mo. All CARMENA patients were treated with VEGFR TKIs only, as ICI combination therapy was not available at the time. In these patients, a reduction in the hazard of death of 20–40% (if they would have been treated with ICI combination therapy, based on the CheckMate-214 study) would have resulted in median OS of 24–28 mo. This is in line with the post hoc OS analysis of mRCC patients with the primary tumour in place in the CM-214 study [30]. This demonstrated median OS of 26.1 mo (95% confidence interval [CI] 14–35 mo) for the ipilimumab + nivolumab arm versus 14.3 mo (95% CI 9.7–23 mo) for the sunitinib arm.

We therefore assume that the median OS for IMDC intermediate/poor-risk synchronous mRCC patients may be up to 28 mo. As in the PrimerX study patients with early systemic disease progression (within 6 mo) are excluded from participation, we estimate that the remaining patients have median OS of 36 mo, when treated with the SOC. The median OS of 36 mo comes down to an event rate per week (lambda) of 1 – (0.5^[1/156 wk]) = 0.0044. We believe that a meaningful deferred local therapy should reduce the hazard of death by at least 25% compared with the SOC (hazard ratio [HR] of 0.75), that is, a 12-mo survival benefit. This would balance the additional treatment burden of local therapy and would result in a median excess in OS of 48 mo in the experimental arm. Furthermore, we estimate that one out of six patients (15%) who are randomised to the experimental arm will refuse any form of local therapy and will therefore be treated by the SOC instead. This noncompliance reduces the measured benefit in an ITT analysis. In addition, a number of patients in the control arm will undergo CN. This also reduces the measured benefit. Based on our 2018–2020 IKNL dataset, we estimate that such “control dilution” will occur in approximately 7% of the cases, as over this period 60 out of 754 synchronous mRCC patients underwent deferred CN. Both noncompliance and control dilution reduce the anticipated HR from 0.75 to 0.7975. After correcting for control dilution, the lambda of the control arm drops from 0.0044 to 0.0043.

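### The planned ITT hazard ratio of 0.7975 allows for refusal but not for patients barred from local therapy by metastatic progression after randomisation

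*Protocol article*

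**What the plan says.** Section 2.7 (Sample size calculation and Bayesian adaptive design) starts from a local therapy that would "reduce the hazard of death by at least 25% compared with the SOC (hazard ratio [HR] of 0.75"). For controls, "we estimate that the remaining patients have median OS of 36 mo, when treated with the SOC". Local therapy "would result in a median excess in OS of 48 mo in the experimental arm", which can only mean a median of 48 months, since the stated gain is 12 months.

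Two allowances are then made. For the experimental arm, "we estimate that one out of six patients (15%) who are randomised to the experimental arm will refuse any form of local therapy". For the control arm, about 7% are expected to undergo CN, taken from 60 of 754 synchronous mRCC patients in the 2018–2020 IKNL data. The resulting ITT hazard ratio is 0.7975.

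Section 2.5 (Experimental intervention) describes another group: "Patients who discontinue their first-line treatment due to progression at metastatic sites in the timeframe between randomisation and local therapy are disqualified for local treatment". They remain in the ITT analysis, and refusers are then mentioned separately as handled in the same way.

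Section 2.6 (SOC treatment) leaves room for CN in controls: "Patients with controlled systemic disease but progression of the primary tumour can be offered deferred CN at the discretion of the treating physician". It does the same for patients with a complete response at metastatic sites.

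On timing, Table 1 requires "Absence of progression at metastatic sites at the time of identification (6 mo after the start of systemic first-line treatment"), whereas the text of section 2.4 says "Since patients are randomised at different time points, between 6 and 18 mo after the start of systemic treatment".

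**The concern.** An ITT hazard ratio is diluted by everyone in the experimental arm who does not receive local therapy, whatever the reason. The plan quantifies one reason (refusal) and creates a second by rule (metastatic progression before treatment) without giving it a rate. Any such patient moves the true ITT hazard ratio closer to 1 than the planned value.

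The control-arm allowance raises a softer question. The 754 patients are described only as having synchronous mRCC. The trial randomises patients whose metastatic disease is controlled after at least 6 months of ICI combination therapy, and section 2.6 permits CN for two kinds of patient with controlled disease. Section 2.7 adjusts survival for this selection (median 28 to 36 months) but does not mention adjusting crossover.

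At stake are the 79.8% power at 700 patients and whether the early checks would reveal the shortfall in time to use the enlarged design.

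**Working it through.** **Inputs from section 2.7.** Control median 36 months; experimental median 48 months (36/0.75); non-receipt n = 0.15; control dilution c = 0.07; final log-rank power 79.8%. Section 2.8 sets the final test at one-sided 0.05.

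**Reproducing the planned hazard ratio.** A ratio of mixed medians fits:

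HR = [(1 − c)·36 + c·48] / [(1 − n)·48 + n·36] = 36.84 / 46.20 = 0.7974.

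The same formula at the contingency inputs (n = 0.25, c = 0.15) gives 37.80/45.00 = 0.840, the article's other figure. So this appears to be the method used, and the planned value is fully explained by 15% and 7%. Nothing is left for progression before local therapy.

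**Events implied by the stated power.** Schoenfeld: d = 4·[(1.645 + z)/ln HR]². With z for 79.8% and HR 0.7975, d ≈ 480 deaths. With 78.6% and HR 0.84 (maximum 1000), d ≈ 782. The article states neither number; they are inferred. Power below is Φ(√(d/4)·|ln HR| − 1.645).

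**Unrounded fractions.** 1/6 = 16.7% and 60/754 = 8.0%:

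HR = 36.955/46.00 = 0.803; power at 480 deaths about 77%. This needs no assumed rate.

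**Adding progression before local therapy.** Let p be the share of non-refusers who progress first, so n = 0.15 + 0.85p, with c kept at 0.07. The documents give no value for p; the range is an assumption.

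| p | n | HR | Power, 480 deaths | Power, 782 deaths |
|---|---|---|---|---|
| 0 | 15.0% | 36.84/46.20 = 0.797 | 80% | 94% |
| 5% | 19.3% | 36.84/45.69 = 0.806 | 76% | 91% |
| 10% | 23.5% | 36.84/45.18 = 0.815 | 72% | 89% |
| 20% | 32.0% | 36.84/44.16 = 0.834 | 63% | 81% |

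The last column shows what the 1000-patient design would deliver if it were triggered. Death counts are held fixed, and progressors are given the average hazard.

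**Sensitivity to the mixing method.** Mixing hazards, HR = [(1 − n)·0.75 + n]/(1 − 0.25c), gives 0.8015 at 15%/7% (power about 78%) and 0.812, 0.823 and 0.845 for the three values of p (about 74%, 69% and 58%). Part of that gap comes from the method rather than from progression, so the size of this point is taken from the mixed medians.

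**Control dilution.** Suppose all 60 deferred CNs came from an eligible 80%, 60% or 40% of the 754. Dilution would be 9.9%, 13.3% or 19.9%, and the HR with 15% refusal 0.805, 0.814 or 0.831. This is an upper bound for each assumed share, because the article does not say who the 60 were.

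**The case against.** The strongest reply is that the plan anticipates dilution beyond its base case. Section 2.7 simulates 25% noncompliance with 15% dilution (HR 0.84, up to 1000 patients, power 78.6%). Table 2 lets the DSMB adjust the maximum sample size when the corrected HR lies between 0.79 and 0.85, and every HR in the main table above falls in that band. This stands: the lower powers apply only if the maximum stays at 700. The protection nevertheless depends on what is counted. Section 2.7 says the checks monitor noncompliance; the Discussion says they monitor refusal rates. Counting refusals alone would miss the progressors. The full protocol may settle this, but the two descriptions differ. Table 2 also prints interim 2 at N = 750, above the 700 maximum; that needs its own correction, and this point does not depend on it.

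Three stronger readings are tempting and not supported:

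- **That control crossover is known to exceed 7%.** It is plausible only. A CN done before randomisation makes a patient ineligible and is not crossover, controls are not told of the intervention, and the article says guidelines do not routinely recommend CN in this setting. The IKNL data may also have been filtered in ways a condensed article omits.
- **That patients already progressed at metastatic sites can enter.** Table 1 read alone might suggest it, but the text of section 2.4 randomises patients without such progression. This is a wording mismatch.
- **That late randomisation causes a measurable loss.** Randomisation and local therapy both end at 18 months, but no distribution of randomisation times is given, so no size can be attached.

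**Conclusion.** The point holds in limited form. The planned ITT hazard ratio of 0.7975 and the 79.8% power rest on refusal and 7% dilution only, while section 2.5 adds a second source of non-receipt that stays in the ITT analysis. The direction is certain if anyone progresses between randomisation and local therapy; the amount is not known.

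The article's own fractions, unrounded, already move the HR to about 0.803 and power to about 77%. With assumed progression of 5% to 20%, the HR is about 0.806 to 0.834 and power about 76% to 63% at a maximum of 700. These figures rest on mixed medians, about 480 deaths, 7% dilution and average hazard among progressors. A higher hazard in progressors would probably dilute further. Higher control crossover would add to the shift but is not demonstrated.

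The contingency design keeps this from being a fatal flaw, provided the checks that trigger it count all non-receipt. The base-case figures should still be corrected.

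**What to change.** - Define noncompliance as any experimental-arm patient who does not receive local therapy, whatever the reason, in the hazard ratio calculation and at interim checks 1 and 2. Align the Discussion with this.
- Use 1/6 and 60/754 unrounded, or correct the fractions if 15% and 7% are intended.
- Re-tabulate control dilution in the IKNL data among patients resembling the PrimerX population.
- State an assumed rate of progression before local therapy, with a range; rerun the simulations and restate the anticipated HR and power.
- Separately, reconcile Table 1 (progression status at 6 months) with the text on who is randomised, and the 6–18 month randomisation window with the local-therapy window ending at 1.5 years. Which rule applies is for the trial team.

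The cost is a re-tabulation of data already held, some wording changes and a simulation rerun. The stated power will be less favourable, and the larger maximum may be needed sooner. No treatment rule has to change for the statistical correction.

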We also ran 10 000 simulations using an HR of 0.84, simulating a weaker HR due to a higher control dilution and noncompliance (ie, respectively, 15% and 25%) and thereby a lambda of 0.0042 in the control arm. In this scenario, we modelled a maximum of 1000 patients, with interim analyses of 350, 450, 550, 650, 750, 850, and 950 patients and adjusted boundaries as summarised in Table 2. All other settings were kept unchanged. The results of this scenario are still satisfactory, and can be implemented after the measurement of control dilution and noncompliance at the second interim. The Data and Safety Monitoring Board (DSMB) will convey after this interim and is responsible for the decision whether to adapt the maximum sample size of the study at this point. Under the HR = 0.84 assumption, the overall Bayesian type I error rate was 4.3% and the empirical power was 69.1% to detect a posterior probability of 70% for HR >0.9. The average sample size was 869 patients under the null scenario (HR = 1) and 892.4 under the alternative scenario (HR = 0.84). The final frequentist log-rank test had a power of 78.6% and a type I error rate of 5.3%.

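### The planned 15% noncompliance and 7% control dilution understate the plan's own fractions (one in six, 60/754), and the stated 79.8% power falls to about 77.5% when those fractions are used

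*Protocol article*

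**What the plan says.** All of this is in section 2.7 of the protocol article (Sample size calculation and Bayesian adaptive design).

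- **Effect before dilution:** local therapy "should reduce the hazard of death by at least 25% compared with the SOC (hazard ratio [HR] of 0.75").
- **Medians:** for the control arm, "we estimate that the remaining patients have median OS of 36 mo, when treated with the SOC". For the experimental arm the text gives 48 months. It calls this an excess, but 36/0.75 = 48, so it is the median itself.
- **Noncompliance:** "we estimate that one out of six patients (15%) who are randomised to the experimental arm will refuse any form of local therapy".
- **Control dilution:** "approximately 7% of the cases, as over this period 60 out of 754 synchronous mRCC patients underwent deferred CN".
- **Result:** "Both noncompliance and control dilution reduce the anticipated HR from 0.75 to 0.7975", with the weekly control event rate falling from 0.0044 to 0.0043. No dilution formula is given.
- **Power:** simulated at 0.7975, "the final one-sided frequentist log-rank test had a power of 79.8% under the alternative hypothesis". The Bayesian criterion reached 76% and the average sample size was 596.8. The design target was 80%.
- **Second scenario:** 15% dilution and 25% noncompliance, giving a hazard ratio of 0.84 and a control rate of 0.0042.
- **Table 2, interim 1:** noncompliance above 15% or control dilution above 7% leads to investigation and action in the recruiting centres.

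**The concern.** Each input is given twice, as a fraction and as a percentage, and the two forms disagree. One in six is 16.7%, not 15%. Sixty out of 754 is 7.96%, which rounds to 8%, not 7%. In both cases the percentage carried forward is the smaller one. Less dilution means a hazard ratio further from 1 and higher calculated power, so the two discrepancies add up.

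Three things depend on these percentages. The main alternative scenario was simulated at the hazard ratio derived from them. The stated power already sits just under the 80% target, so it has no margin for a further loss. The same percentages also serve as action thresholds at interim 1. The Discussion notes that earlier oncology trials of this type underestimated refusal and had to enlarge their samples, and names this as a risk here.

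**Working it through.** **1. Reproduce the plan's figure.** Weight the stated medians by the stated percentages.

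- Experimental arm: 0.85 × 48 + 0.15 × 36 = 46.2 months.
- Control arm: 0.93 × 36 + 0.07 × 48 = 36.84 months.
- Hazard ratio: 36.84/46.2 = 0.7974 (stated 0.7975).

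The same rule fits the other stated figures:

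- Second scenario: control 0.85 × 36 + 0.15 × 48 = 37.8; experimental 0.75 × 48 + 0.25 × 36 = 45; ratio 0.8400 (stated 0.84).
- Weekly control rates from medians of 36.84 and 37.8 months, by the plan's formula 1 − 0.5^(1/weeks) with 36 months = 156 weeks: 0.00433 and 0.00422 (stated 0.0043 and 0.0042).

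The plan gives no formula, but averaged medians account for all four figures.

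**2. Put in the plan's fractions.** 1/6 = 0.1667; 60/754 = 0.0796.

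- Averaged medians: control 36 + 12 × 0.0796 = 36.95; experimental 48 − 12/6 = 46.0; ratio 0.8034.
- Weighted hazards: [(5/6) × 0.75 + 1/6] / [1 − 0.25 × 0.0796] = 0.7917/0.9801 = 0.8077.
- Exact exponential mixtures, event-weighted average, 5-year minimum follow-up, accrual assumed to take 0 to 5 years: 0.8052 to 0.8057.

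**3. Convert to power.** The accrual rate is not given, so the adaptive simulation cannot be repeated. As an approximation, take the number of deaths D at which the Schoenfeld formula returns the stated 79.8% at 0.7975, one-sided 5%:

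D = 4 × [(1.645 + 0.834)/0.2263]² ≈ 480.

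Then power = Φ(√D/2 × |ln HR| − 1.645), with √480.25/2 = 10.957.

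| Inputs and rule | HR | Power |
|---|---|---|
| Stated | 0.7975 | 79.8% |
| 60/754 only, medians | 0.7999 | 78.9% |
| 1/6 only, medians | 0.8009 | 78.5% |
| Both fractions, medians | 0.8034 | 77.5% |
| Both fractions, exact mixture | 0.8052 to 0.8057 | 76.7% to 76.5% |
| Both fractions, weighted hazards | 0.8077 | 75.6% |

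Worked line for medians with both fractions: 10.957 × 0.2189 − 1.645 = 0.754, and Φ(0.754) = 0.775.

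**4. Scale in patients.** Holding power fixed, the sample size scales as (ln 0.7975/ln HR)². The 700 would become about 748 at 0.8034 and about 786 at 0.8077.

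**The case against.** The percentages are planning guesses, worded as estimates and as approximate. The plan also allows for error in them: it simulates a much worse case (25% and 15%, up to 1000 patients), monitors the actual rates early, and lets the Data and Safety Monitoring Board change the maximum sample size. This stands as far as the conduct of the trial is concerned, and it is why the point is moderate. It does not make the stated power correct for the stated fractions. Nor does it explain why 60/754, offered as the basis for the dilution estimate, becomes 7%.

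A reader might go further and infer that 0.7975 does not follow from 15% and 7%. Weighted hazards give 0.7875/0.9825 = 0.8015 at those inputs, and they give 0.7975 only if dilution is 5%. The document does not support this reading. It names no weighted-hazards method and no 5% figure, while averaged medians reproduce both hazard ratios and both control rates at the stated inputs. Weighted hazards are also an approximation: the exact mixture at 15% and 7% is 0.7991 to 0.7996, slightly closer to 0.7975 than to 0.8015. At those inputs the choice of rule moves power by at most about 1.6 points (79.8% to 78.2%).

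A reader might also infer that the interim 2 limits of 0.79 and 0.85 rest on a wrong figure. The document does not derive those limits from 0.7975, so this cannot be shown.

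**Conclusion.** The point holds for the inputs, not for the dilution step. Section 2.7 contradicts itself on both rates, each time in the direction that favours power. At the plan's own fractions the diluted hazard ratio is about 0.803 by the rule that reproduces the plan, and up to 0.808 with weighted hazards. Final log-rank power is then about 77.5%, down to about 75.6%: a loss of 2.3 to 4.2 points from 79.8%. For comparison, the simulation error of the stated figure with 5000 runs is √(0.798 × 0.202/5000) ≈ 0.6 points.

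The power figures rest on a fixed number of deaths (480) calibrated to the stated result, not on a rerun of the adaptive design. The effect on the 76% Bayesian power and on the average sample size was not computed.

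The interim 1 consequence needs no model. Rates of 16.7% and 8.0% exceed both Table 2 triggers, so centres would be investigated for behaviour that the source fractions predict.

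**What to change.** 1. Reconcile one in six with 15%, and 60/754 with 7%, and state the dilution formula.
2. Rerun the FACTS alternative scenario at the resulting hazard ratio (about 0.803 with averaged medians if the fractions are kept). Restate the log-rank power, the Bayesian power and the average sample size.
3. Align the interim 1 triggers in Table 2 with the reconciled rates.
4. If 15% and 7% are the intended assumptions, correct the fractions or justify departing from them, and report power at 16.7% and 8.0% alongside.

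The cost is one simulation rerun and corrected text, with a slightly less favourable stated power. The correction does not in itself require more patients; whether the lower power is acceptable at a maximum of 700 is then an open decision for the sponsor.
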